### Sample size

The primary outcomes of this clinical trial are telomere length, measured in kilobases using quantitative PCR, and telomerase activity, quantified using an ELISA-based TRAP assay. Both are continuous biological markers that reflect cellular aging processes. Sample size estimation was conducted using the formula for comparing two independent means, appropriate for continuous outcomes. Based on pilot findings reported by Ornish et al. (41), a mean difference of 0.5 kb in telomere length between groups was considered clinically relevant, with a standard deviation (SD) of 0.7 kb. A significance level of *α* = 0.05 and power of 80% (*β* = 0.20) were applied in the calculation. Using these parameters, the required sample size per group was obtained, and after accounting for a 10% dropout rate, the final required sample size was determined to be 37 participants per group, resulting in a total of 74 participants for the study. Although Ornish et al. (41) studied men with prostate cancer—a different population from our healthy older adults—we used this data as it provided the most relevant preliminary estimate of variability and effect size available. We acknowledge that this may limit the precision of our sample size calculation and will interpret our findings accordingly. With a significance level of *α* = 0.05 and power of 80% (*β* = 0.20), the required sample size per group was calculated, and after accounting for a 10% dropout rate, the final sample size was determined to be 37 participants per group, for a total of 74 participants. To further strengthen the validity of these assumptions, a dose-finding and feasibility phase will be conducted prior to the full RCT. Data generated from this phase will be used to validate and refine the expected effect sizes, particularly for telomerase activity and cognitive outcomes, thereby enhancing the robustness of the final trial estimates.

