### Storage, packaging, and dispensing of investigational supplement

#### Outcome measurements

##### Primary outcomes

The following primary outcome measures is assessed at baseline, 45 and 90 days:

Telomerase activity and telomerase length of blood mononuclear cells of participants measured using qualitative polymerase chain reaction (QPCR).

The following secondary outcomes measures are assessed at baseline, 45 and 90 days:

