### Outcome assessor blinding

All primary and secondary outcomes will be measured in both the BMFD and placebo groups using standardized procedures.

Primary outcomes (telomerase activity and telomere length) will be measured using laboratory assays with coded samples, ensuring objective assessment and minimizing bias.

Secondary outcomes [cognitive function, neurophysiological function, and health-related quality of life (HRQoL)] will be administered identically to both groups. Where feasible, scoring of subjective outcomes will be performed by assessors blinded to group allocation to reduce potential measurement bias (see Table 2).

**Table 2 tab2:** Study procedures.

Study procedures/assessments	Screening (Week 1)	Baseline (Week 0)	Week 6	Week 12 (Endline)
Enrollment				
Eligibility screening	✓			
Informed consent	✓			
Recruitment	✓			
Randomization		✓		
Interventions				
ARM 1: BMFD administration		✓	✓	✓
ARM 2: Placebo administration		✓	✓	✓
Assessments/investigations				
MoCA (cognitive assessment)		✓	✓	✓
Constitutional (*Prakriti*) analysis		✓		
Nerve conduction test (NCT)		✓		✓
Electroencephalography (EEG)		✓		✓
Telomere length		✓		✓
Telomerase activity		✓		✓
Health-related quality of life (HRQoL)		✓	✓	✓
Safety monitoring				
Adverse event assessment		✓	✓	✓

✓ indicates the procedure performed at the specified timepoint.

Baseline = prior to initiation of intervention.

Week 12 represents end-of-treatment follow-up.

HRQoL—health-related quality of life.

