### Method of data analysis

For both primary and secondary outcome measures, mean values at baseline and study completion, as well as mean differences, will be compared across the two study arms using ANOVA (Analysis of Variance) or the non-parametric Kruskal–Walli’s test, depending on the data’s normality. Within each treatment arm, changes in primary and secondary outcomes before and after the intervention will be analyzed using either paired-sample *t*-tests or the non-parametric Wilcoxon signed-rank test, based on the distribution of the data. For all normally distributed outcomes, 95% confidence intervals will be calculated. Categorical variables will be analyzed between groups using the Chi-square test. Potential confounding factors will be adjusted using ANCOVA, with adjusted mean values and corresponding confidence intervals subsequently calculated and reported. Regarding missing data, instead of the last observation carried forward, multiple imputation techniques will be employed to handle missing outcome data, ensuring a more robust and unbiased estimation. Statistical analysis will be conducted using the SPSS software (version 20.0), and the level of significance will be set at *α* = 0.05. In cases of missing outcome data, the most recent available values of the outcome measures will be used as replacements. Intention-to-treat analysis will be applied for all efficacy and safety outcomes. Additionally, per-protocol analysis will be conducted for efficacy outcomes, including only participants who complete the follow-up.

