### Statistical analysis

The statistical analysis plan has been developed to align with the study objectives and ensure rigorous evaluation of outcomes. Descriptive statistics will be used to summarize baseline characteristics across study arms. Continuous primary and secondary outcomes will be assessed for normality prior to analysis. Between-group comparisons of mean changes from baseline to study completion will be conducted using analysis of variance (ANOVA) for normally distributed data or the Kruskal–Wallis test for non-normal data. Within-group pre–post changes will be analyzed using paired-sample *t*-tests or Wilcoxon signed-rank tests, as appropriate.

To account for baseline imbalances and potential confounding factors such as age, sex, and baseline outcome values, analysis of covariance (ANCOVA) will be applied, with adjusted mean differences reported alongside 95% confidence intervals. Categorical variables will be compared between groups using the Chi-square test or Fisher’s exact test, as appropriate.

Missing outcome data will be handled using multiple imputation methods to minimize bias and improve the robustness of estimates. The primary analysis will follow the intention-to-treat principle for all efficacy and safety outcomes, with a secondary per-protocol analysis conducted for efficacy outcomes among participants who complete the follow-up assessments. All statistical analyses will be performed using SPSS software (version 20.0), with a two-sided significance level set at *α* = 0.05.

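### The protocol gives two incompatible rules for missing outcome data, multiple imputation and carry-forward, so the intention-to-treat primary result is not uniquely prespecified

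*Protocol article*

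**What the plan says.** Three statements in the protocol article govern missing outcome data.

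- Method of data analysis, first statement: "instead of the last observation carried forward, multiple imputation techniques will be employed to handle missing outcome data".
- Method of data analysis, two sentences later: "In cases of missing outcome data, the most recent available values of the outcome measures will be used as replacements".
- Statistical analysis: "Missing outcome data will be handled using multiple imputation methods to minimize bias and improve the robustness of estimates".

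The rule matters because of the analysis set: "The primary analysis will follow the intention-to-treat principle for all efficacy and safety outcomes". Drop-outs stay in the primary comparison and need a value. The quantity compared is the mean change from baseline to study completion.

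The visits for the primary outcomes are given in two ways. The section Primary outcomes says: "The following primary outcome measures is assessed at baseline, 45 and 90 days". The Study design paragraph of the abstract gives the same three times. Table 2 ticks telomere length and telomerase activity at baseline and Week 12 only, and leaves Week 6 empty.

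**The concern.** Replacing a missing outcome with the latest available value is last observation carried forward, the method that the same paragraph has just set aside. Neither sentence is limited to a sensitivity analysis, an outcome or an analysis set, so both cannot be followed.

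Missing values are expected. The sample size allows for 10% dropout, and participants who need other medication have to leave the trial. As the text stands, the choice between the rules could be made after the data are seen and still be defended from the protocol.

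The two rules also behave differently. Carry-forward treats a filled-in value as if it had been observed. When the only earlier value is the baseline, it scores the participant as unchanged. That pulls the estimate toward no difference when a real effect exists. It can also create a small difference when both arms drift and dropout is unequal.

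**Working it through.** **1. The plan's own figure.** Inputs from Sample size: "a mean difference of 0.5 kb in telomere length between groups was considered clinically relevant", SD 0.7 kb, α = 0.05, power 80%, dropout 10%. The two-sided test is stated in Statistical analysis.

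n per arm = 2 × [0.7 × (1.960 + 0.842) / 0.5]² = 30.8, so 31. Dividing by 0.9 gives 35. The t-based version needs 32, which inflates to 36. The stated 37 is within one or two participants per arm of these, and 37 is used below.

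**2. Can the rules be read together?**

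| Place | Rule | Scope stated |
|---|---|---|
| Method of data analysis, first statement | Multiple imputation, carry-forward rejected | Missing outcome data |
| Method of data analysis, later sentence | Latest available value | Missing outcome data |
| Statistical analysis | Multiple imputation | Missing outcome data |

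The scope is the same in all three, so no reading reconciles them.

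**3. What carry-forward does under each schedule.** Let d be the dropout share, with a true difference of 0.5 kb arising wholly as change on active.

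- Table 2 schedule: the only value before Week 12 is baseline, so each drop-out's change is 0. Expected difference = (1 − d) × 0.5. At d = 0.10 this is 0.45 kb, with 0.10 × 37 ≈ 4 drop-outs per arm.
- Text schedule: let h be the share of drop-outs who leave after day 45, and f the fraction of the effect reached by then. Expected difference = 0.5 × (1 − d + d·h·f). At d = 0.10:
  - h = 0.5 and f = 0.5 to 1 gives 0.4625 to 0.475 kb;
  - h = 1 and f = 0.5 to 1 gives 0.475 to 0.50 kb.

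**4. Power under the Table 2 schedule.** Assumptions not in the protocol: SD of change 0.7 kb (this follows from SD 0.7 and a baseline–follow-up correlation of 0.5, since 0.7 × √[2(1 − 0.5)] = 0.7), dropout unrelated to outcome, and no change on placebo.

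Variance per arm under carry-forward = (1 − d) × 0.49 + d(1 − d) × c², where c is the arm's mean change.

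*10% in both arms (the planned rate).*
- Active: 0.9 × 0.49 + 0.09 × 0.25 = 0.4635. Placebo: 0.441.
- SE = √(0.9045 / 37) = 0.156. Power = Φ(0.45 / 0.156 − 1.96) ≈ 82%.
- Observed cases, 33.3 per arm: SE = 0.7 × √(2 / 33.3) = 0.172. Power = Φ(0.50 / 0.172 − 1.96) ≈ 83%.
- Simulation with t-tests (8,000 replicates): 81.1% against 81.5%.

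*10% placebo and 20% active (assumed, not in the protocol).*
- Difference = 0.8 × 0.5 = 0.40 kb. Active variance: 0.8 × 0.49 + 0.16 × 0.25 = 0.432. Placebo: 0.441.
- SE = √(0.873 / 37) = 0.154. Power = Φ(0.40 / 0.154 − 1.96) ≈ 74%. Simulation: 73.6%, against 79.5% for observed cases.
- If the effect is +0.25 on active and −0.25 on placebo: 0.25 × 0.8 + 0.25 × 0.9 = 0.425 kb.
- If it is wholly a decline on placebo: 0.5 × 0.9 = 0.45 kb.

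**5. Bias away from zero.** Suppose there is no true difference, both arms fall by 0.1 kb, and dropout is 5% on placebo and 15% on active. Carry-forward gives 0.85 × (−0.1) − 0.95 × (−0.1) = +0.01 kb. This is small, but it favours active with no effect present.

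**The case against.** The strongest reply is that the intended rule can be recognised. The protocol rejects carry-forward by name, and the section that defines the primary analysis specifies multiple imputation alone. Two of three statements agree, and the third may be leftover text. That is plausible and it points to the right correction, but the sentence is current and unqualified, so an analyst could still rely on it.

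A second reply is that the effect is small. This stands at the planned dropout: 0.05 kb and about one point of power or less. The larger loss needs 20% dropout on active, which the protocol does not anticipate, and 0.40 kb is the low end of a range that depends on which arm changes. The comparator in these figures is observed cases, not multiple imputation itself.

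A reader might infer that carry-forward would score every drop-out as unchanged. The documents do not support that without a condition. It follows from Table 2, but not from the schedule in the abstract and in Primary outcomes, where a participant lost after day 45 carries a day-45 value.

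A reader might also fault the absence of an imputation model or a departure-from-assumption sensitivity analysis. Those details commonly belong to the statistical analysis plan, which is not shown, so they are no finding.

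Nor can carry-forward be kept on the ground that it is always conservative. The abstract calls the trial superiority, while Methods (Study design) and the Discussion call it non-inferiority, where shrinkage toward no difference can make the arms look falsely alike.

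**Conclusion.** Wrong as written. Two rules that cannot both be applied govern the same missing outcome data, and the later section does not settle the matter by withdrawing one. The main harm is that the intention-to-treat primary estimate is not uniquely prespecified, rather than a large bias.

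If the carry-forward sentence were followed at the planned 10% dropout, the expected telomere difference would be 0.45 kb under Table 2, and up to 0.50 kb under the 45- and 90-day schedule, against a true 0.50 kb. Under Table 2 power would be about 81% against 82%. With an assumed 10% placebo and 20% active dropout under Table 2, the estimate would be 0.40 to 0.45 kb, with power of about 73–74% at the lower end.

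The power figures rest on an SD of change of 0.7 kb, dropout unrelated to outcome, 37 per arm and, except where stated, the whole effect arising on active. The protocol does not state that its SD of 0.7 kb is an SD of change. The contradiction itself depends on none of these assumptions.

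**What to change.** 1. In Method of data analysis, delete the sentence that replaces missing outcomes with the latest available value, or label it explicitly as a sensitivity analysis.
2. Keep multiple imputation as the single primary rule, in line with Statistical analysis.
3. Reconcile the primary-outcome visits in Table 2 with those in the abstract and in Primary outcomes, so that it is clear whether a day-45 value exists.

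The first two changes cost one sentence. The third is a correction to a table or to the text. None of them changes the stated sample size. All should be made before unblinding.

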### Safety assessment

Each participant will undergo hematological and biochemical assessments, including fasting blood sugar (FBS), full blood count (FBC), erythrocyte sedimentation rate (ESR), aspartate aminotransferase (AST), alanine aminotransferase (ALT), and serum creatinine/glomerular filtration rate (GFR), along with a comprehensive urine analysis, both before and after the intervention. These evaluations primarily serve as a safety assessment measure. Adverse events experienced by participants will be systematically recorded on a weekly basis by investigators during scheduled visits to the clinical trial center. Additionally, participants will be instructed to document any adverse reactions in their diaries and promptly report them using the designated contact numbers. In the event of unexpected symptoms or concerns, they will be advised to visit the trial center at the Faculty of Indigenous Medicine for further evaluation. Any serious adverse events will undergo thorough assessment and will be reported to the Ethics Review Committee (ERC) of the Faculty of Indigenous Medicine within five working days. Although no severe adverse reactions are anticipated with BMFD Herbal supplement, in cases where an adverse reaction necessitates hospitalization, appropriate medical care and expert management will be ensured. If at any point the safety of trial participants can no longer be guaranteed or new scientific evidence emerges indicating potential risks, the clinical trial will be prematurely terminated.

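### Safety is assigned to intention-to-treat alone, with no exposed, as-received set, which can dilute a safety difference if anyone never doses or receives the wrong product

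*Protocol article*

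**What the plan says.** Two sections of the protocol article set the analysis population for safety, and they agree. Method of data analysis: "Intention-to-treat analysis will be applied for all efficacy and safety outcomes". Statistical analysis: "The primary analysis will follow the intention-to-treat principle for all efficacy and safety outcomes".

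The only other population named is for efficacy. In Method of data analysis, a "per-protocol analysis will be conducted for efficacy outcomes, including only participants who complete the follow-up"; Statistical analysis says the same in substance. Neither section names a population defined by exposure or by product received.

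On missing data, Method of data analysis gives two rules. One is that "multiple imputation techniques will be employed to handle missing outcome data". A later sentence in the same paragraph reads: "In cases of missing outcome data, the most recent available values of the outcome measures will be used as replacements". Statistical analysis gives only the first: "Missing outcome data will be handled using multiple imputation methods to minimize bias and improve the robustness of estimates". None of these sentences mentions safety data, either to include or to exempt them.

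Under Safety assessment, blood and urine tests are done "both before and after the intervention. These evaluations primarily serve as a safety assessment measure", and adverse events are recorded weekly.

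**The concern.** Intention-to-treat suits efficacy because it preserves the randomised comparison and is usually conservative for a superiority claim. For harm, the same pull towards no difference is not conservative. Randomised people who never took the product cannot have been harmed by it but remain in the denominator, and anyone given the wrong product has their events counted under the allocated one. No other safety analysis is stated that would reveal this. Because the article fixes the population twice, a later exposed-only set would contradict it, so this is not a gap left to a separate analysis plan.

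The second strand is missing laboratory data. Some exits are linked to possible harm: Safety monitoring and stopping criteria sets laboratory thresholds for discontinuation, and Inclusion and exclusion criteria requires anyone who needs other medication to leave the trial. With tests scheduled only before and after the intervention, a person who leaves early may have no later value. If the general missing-data rules are then applied, the gap is filled either by a model fitted mainly to those who stayed or by the person's own last value, which may predate treatment.

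**Working it through.** **Plan's own figure.** The denominator used below is 37 per arm (Sample size). From the stated inputs (difference 0.5 kb, SD 0.7 kb, two-sided alpha 0.05, power 80%), n = 2 × [0.7 × (1.960 + 0.842) / 0.5]² = 30.8, so 31 per arm, and 31/0.9 = 34.4, so 35. A t-based calculation gives 32, and 32/0.9 = 35.6, so 36. Both are close to the stated 37, which is taken as given. The point does not depend on it.

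**Inputs not in the documents.** The article gives no number of non-starters, dispensing errors, event risks or harm-related exits. All such values below are assumptions chosen to show a range.

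**Step 1: one-arm proportion.** Assume six BMFD participants with an event and 2 to 4 of 37 who never dose.
- Exposed set, 2 non-starters: 6/35 = 17.1%.
- Exposed set, 4 non-starters: 6/33 = 18.2%.
- Intention-to-treat: 6/37 = 16.2%.
- Ratios: 35/37 = 0.946 and 33/37 = 0.892, so the understatement is 5% to 11% in relative terms, or about 1 to 2 percentage points.

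**Step 2: between-arm difference.** Assume event risks of 30% on BMFD and 10% on placebo or no product (true difference 20 points), 37 per arm, u never exposed in the BMFD arm, and x in each arm who took the other product.
- BMFD arm as allocated = [(37 − u − x) × 0.30 + (u + x) × 0.10] / 37
- Placebo arm as allocated = [(37 − x) × 0.10 + x × 0.30] / 37

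| u | x | Difference by allocation | Share of true |
|---|---|---|---|
| 0 | 0 | 20.0 points | 100% |
| 1 | 0 | 19.5 points | 97% |
| 4 | 0 | 17.8 points | 89% |
| 0 | 2 | 17.8 points | 89% |
| 4 | 2 | 15.7 points | 78% |

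**Step 3: missing end-of-treatment laboratory values.** The planned 10% dropout is 3.7 of 37, about 4. Assume 4 BMFD participants lack the later value, 10% of BMFD completers are abnormal, and placebo is 5% with nothing missing.
- If half of the leavers are abnormal: true risk (33 × 0.10 + 4 × 0.50)/37 = 14.3%, true difference 9.3 points.
- If all are: (33 × 0.10 + 4 × 1.00)/37 = 19.7%, true difference 14.7 points.
- If leavers resemble completers: 10%, difference 5.0 points.
- Imputation modelled on completers gives 10%, difference 5.0 points, in all three cases.
- Carrying forward a normal pre-treatment value gives (33 × 0.10 + 4 × 0)/37 = 8.9%, difference 3.9 points.
- Leaving the four out gives 10%, difference 5.0 points.

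Both stated rules can hide harm when leaving is related to it. Analysing observed values alone does not cure this either.

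**The case against.** Much can be said on the other side.

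- **Imputation of safety data is not stated.** A reader might infer it from the unqualified reference to missing outcome data, since the same section also speaks of safety outcomes. But the outcome lists contain no safety measure, and intention-to-treat decides the arm in which a person is counted; it does not require a value to be filled in. The inference is possible for laboratory values and weak for adverse-event counts. This stands: all that can be said is that safety data are not exempted.
- **The mechanism is not settled.** Under the most-recent-value sentence, gaps are filled from the person's own data and not from those who tolerated the product. This stands too, and makes the contradiction part of the point.
- **Stopping for a laboratory threshold implies an observed abnormal value**, and for related serious events the article stops the product without ending follow-up. This narrows the laboratory concern to people who leave without a later test, chiefly through the other-medication rule.
- **Dilution is not inevitable.** A reader might conclude that any harm must be diluted. It need not be: with no non-starters, no swaps and no harm-related exits, the results coincide. Product is handed out by allocation by an independent dispenser, and a run-in precedes randomisation, so numbers may be small.
- **Pooling of on-product and later events.** A reader might infer this from the follow-up to day 90. No section says so, and tabulation by period is ordinary analysis-plan detail.
- **Monitoring gives separate protection.** Individual laboratory triggers, a suspension rule and board review of imbalance all exist. They limit the consequence but do not replace the final safety comparison.

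None of this removes the core: the article fixes one population for safety, and it is not based on exposure.

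**Conclusion.** The point holds in a limited form. Both analysis sections make intention-to-treat the only population for safety and confine the second population to efficacy. This can dilute the BMFD-placebo safety difference if anyone never doses or takes the wrong product. Under the assumed scenarios the effect is a 5% to 11% relative understatement of a one-arm event rate, or a between-arm difference shown at 78% to 97% of its true size. It is nil if neither occurs.

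The missing-data strand is conditional. It needs the general rules to be applied to laboratory values and exits to be related to harm. In the assumed example a true difference of 9.3 to 14.7 points would appear as 5.0 under imputation from completers, or 3.9 if normal pre-treatment values were carried forward. It would be undistorted under imputation if leavers resembled completers. The contradiction between the two rules is in the text whatever these assumptions.

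The change is worth making because it is cheap and the possible error favours the product. The sample size is unaffected.

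**What to change.** Amend Method of data analysis and Statistical analysis together:

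1. Keep intention-to-treat for efficacy. Analyse safety in all participants who took at least one dose, grouped by the product actually taken, and keep the intention-to-treat safety table as supportive.
2. State that adverse events are not imputed.
3. Include in the laboratory safety analysis any value obtained at or after stopping, and report missing laboratory values and reasons for withdrawal by arm. This matters because an observed-data analysis of laboratory values shares the completer bias shown above.
4. Reconcile the two missing-data sentences in Method of data analysis, and say whether the surviving rule covers laboratory safety values.

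Cost: a few sentences and one more table. A small downside is that the main safety comparison would not be strictly by randomised group if anyone received the wrong product; the supportive intention-to-treat table covers that.
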